### 6.6.1. Medical Approach to Withdrawal

In all cases in which the treatment is concluded prematurely for any reason, detailed information will be given about the date and reasons of the discontinuation to the promoter.

The investigator will facilitate the necessary medical support to the patient who discontinues the study prematurely due to treatment failure or to the appearance of an adverse event or a related concurrent illness.

In case of virologic failure,

- Genotypic resistance testing will be performed to all participants experiencing virologic failure during the study.
- A salvage regimen will be optimized according to genotypic resistance testing and previous antiretroviral treatment history.

## 6.7. PRE-RANDOMIZATION LOSSES

Do not proceed, patients who do not fulfill the selection criteria, will not be asked to participate in the study.

## 6.8. APPROXIMATE DURATION OF THE RECRUITMENT PERIOD

24 weeks.

# 7.- TREATMENT DESCRIPTION

## 7.1. EXPERIMENTAL AND CONTROL TREATMENTS

Patients in the control group will be receiving a standard triple-drug HAART composed of marketed drugs that will include a PI plus at least two NRTIs.

Patients in the experimental group will be receiving etravirine plus at least two NRTIs.

The experimental drug is etravirine, administered in a 100 mg tablet dissolved in water, 4 tablets (400mg) every 24 hours. The tablet formulation also contains Hypromellose, Microcrystalline cellulose, Colloidal anhydrous sílica, Croscarmellose sodium, Magnesium stearate, Lactose monohydrate.

## 7.2. SUPPLY, PACKAGING, LABELING AND STORAGE

All antiretroviral treatments will be administered by the Pharmacy Service in the marketed format.

All of the medication for the clinical study should be stored in a secure place during the study.

## 7.3. DOSAGE, INTERVAL, ROUTE AND FORM OF ADMINISTRATION

All candidates will be receiving a triple-drug standard HAART with marketed drugs and at approved standard doses that will include a PI plus at least two NRTIs.

Experimental group: switch from the PI to etravirine*.

Control group: to continue with their same regimen.

*Etravirine: 4 tablets of 100mg each (400mg), dissolved in water, every 24h

All the drugs will be orally administered.

## 7.4. MODIFICATION OF THE TREATMENT REGIMEN

No changes in treatment guidelines are foreseen.

## 7.5. CONCOMITANT TREATMENTS

All other treatments apart from antiretroviral medication administered during the study period will be considered concomitant treatments and should be documented in the CRF.

It is remembered that the patients who participate in the study should not continue any concomitant treatment without the knowledge and permission of the investigator.

Following known interactions with medicinal products are listed:

| **Medicinal product** | **Clinical comment** |
| --- | --- |
| Digoxin | It is recommended that digoxin levels be monitored when digoxin is combined with etravirine. |
| Amiodarone  Bepridil  Disopyramide  Flecainide  Lidocaine (systemic)  Mexiletine  Propafenone  Quinidine | Caution is warranted and therapeutic concentration monitoring, if available, is recommended for antiarrhythmics when co-administered with etravirine. |
| Clarithromycin | Alternatives to clarithromycin should be considered for the treatment of *Mycobacterium avium* omplex. |
| Warfarin | It is recommended that the international normalised ratio (INR) be monitored when warfarin is combined with etravirine. |
| Rifampicin  Rifapentine | Combination not recommended. |
| Rifabutin | The combination of etravirine and rifabutin should be used with caution due to the risk of decrease in etravirine and rifabutin exposures. |
| Diazepam | Alternatives to diazepam should be considered. |
| Dexamethasone (systemic) | Systemic dexamethasone should be used with caution or alternatives should be considered, particularly for chronic use. |
| St John's wort *(Hypericum perforatum)* | Combination not recommended. |
| Atorvastatin | The combination of etravirine and atorvastatin  can be given without any dose adjustments, however, the dose of atorvastatin may need to be altered based on clinical response. |
| Fluvastatin  Lovastatin  Pravastatin  Rosuvastatin  Simvastatin | Dose adjustments for these HMG Co-A reductase inhibitors may be necessary. |
| Cyclosporine  Sirolimus  Tacrolimus | Co-administration with systemic immunosuppressants should be done with caution because plasma concentrations of cyclosporine, sirolimus or tacrolimus may be affected when co-administered with etravirine. |
| Sildenafil  Vardenafil  Tadalafil | Concomitant use of PDE-5 inhibitors with etravirine may require dose adjustment of the PDE-5 inhibitor to attain the desired clinical effect. |

## 7.6. COMPLIANCE

The investigator is to ask the patient about treatment adherence to antiretroviral and concomitant treatment (particularly lipid-lowering drug agents) and this data is to be written in the clinical record. This data will be to guarantee the compliance.

## 7.7. NORMS FOR MANIPULATING THE STUDY TREATMENTS

Etravirine:

Store in the original bottle. Keep the bottle tightly closed in order to protect from moisture. Do not remove the desiccant pouches.

# 8.- TRIAL CONDUCTION AND RESPONSE EVALUATION

## 8.1. CRITERIA FOR RESPONSE EVALUATION

### 8.1.1. Principal Study Variable

Viral load at week 48.

Virologic failure is defined as an increase in HIV RNA >50 copies/mL in 2 determinations within 1 month. The first date with VL > 50 copies/mL will be used to calculate time to virologic failure.

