## 6.6. WITHDRAWAL AND DROPOUT CRITERIA

The patients will complete the clinical study before the stipulated time in the following circumstances:

- Virologic failure: it is defined as an increase in VL > 50 copies/mL on two consecutive visits.
- Interruption of treatment due to adverse events, intolerance or poor adherence during the study.
- Concurrent process or illness which in the opinion of the investigator requires the withdrawal of the patient.
- The patient does not wish to continue in the study.

If the study must be interrupted prematurely, all of the materials should be returned to the sponsor, at the *Lluita Contra la SIDA Foundation.*

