### 8.1.2. Secondary Study Variables

- CD4+/CD8+ T lymphocytes count.
- Genotypic test if virologic failure occurs.
- Lipid profile: total, HDL-, LDL-cholesterol and triglyceride levels
- Administration of lipid-lowering drugs throughout the study (new administrations or the withdrawal of previous lipid-lowering drugs).
- Cardiovascular risk assessed by the SCORE equation
- Patient’s satisfaction assessed using a 100 mm analogue visual scale.
- Adverse events related to antiretroviral treatment (Toxicity)

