### 8.1.3. Endpoints

**Primary objective:**

To compare the virological efficacy of etravirine-based regimen with standard PI-containing regimens.

- The percentage of patients who experienced virologic failure throughout the 48 weeks of the study. Virologic failure will be defined as an increase in HIV RNA >50 copies in 2 determinations within 1 month.
- Time to virologic failure, defined as an increase in HIV RNA >50 copies in 2 determinations within 1 month. The first date with VL > 50 will be used to calculate time to virologic failure.
- Determination of antiretroviral resistance at the time of virological failure and comparison with baseline.

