## 12.2. RESPONSE EVALUATION

The response evaluation is going to be done per-protocol, an interim analysis will be performed will be performed when 75% of subjects reach week 24 of follow-up , the final analysis will be based on patients completing the entire 48 weeks of treatment.

The statistical significance of the longitudinal changes in the HIV RNA viral load and lipid parameters are going to be assessed by the calculation of the slope of decay and compared using t-student, Wilcoxon or Mann-Whitney distinguishing between treatment groups and/or other relevant baseline factor.

HIV RNA viral load is going to be transformed by the log10 and if necessary, other transformations of the data are going to be considered.

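### The principal variable in 8.1.1 (week-48 viral load) is not among the three unranked endpoints that 8.1.3 gives the primary objective, and it would miss most earlier virologic failures

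*Protocol*

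**What the plan says.** Section 8.1.1 gives the principal study variable as "Viral load at week 48". Section 1.14 of the summary says only that it is viral load, with no time point. Neither states a scale (mean log10 value, or proportion below 50 copies/mL). Under the same heading, 8.1.1 adds a failure definition: "Virologic failure is defined as an increase in HIV RNA >50 copies/mL in 2 determinations within 1 month".

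Section 8.1.3 lists three endpoints under the primary objective:

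- "The percentage of patients who experienced virologic failure throughout the 48 weeks of the study"
- "Time to virologic failure, defined as an increase in HIV RNA >50 copies in 2 determinations within 1 month"
- "Determination of antiretroviral resistance at the time of virological failure and comparison with baseline"

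They are not ranked, none is called primary, and week-48 viral load is not among them. Section 8.1.2 places resistance among the secondary variables: "Genotypic test if virologic failure occurs".

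Section 6.6 makes virologic failure a reason for leaving the study early, under a different definition: "Virologic failure: it is defined as an increase in VL > 50 copies/mL on two consecutive visits". Section 12.2 plans a per-protocol evaluation in which "the final analysis will be based on patients completing the entire 48 weeks of treatment". The only viral-load comparison it describes is of slopes, by t, Wilcoxon or Mann-Whitney tests.

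**The concern.** A reader cannot tell which comparison answers the primary objective. Section 8.1.1 points to a value at one time point, 8.1.3 to an event at any time in 48 weeks, and 12.2 to a slope. The analysis section does not settle the matter, because a slope comparison yields neither a failure percentage nor a time to failure.

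The difference matters because failing ends participation. A measure taken only at week 48, in those still present, leaves out the patients whose outcome the primary objective is meant to count. If more patients failed early on one arm, a week-48 comparison among those who remain could look similar between arms. The trial is open-label and small, so a choice left open until data are seen could affect what is reported as the main finding.

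**Working it through.** The protocol has no figure to reproduce here: 12.4 gives 40 patients (20 per arm) without alpha, power, effect size or event rates. The check compares the sections and then illustrates the size of the gap.

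**Step 1. Which endpoints share an event?** In 8.1.3, the percentage with failure and the time to failure use the same definition, so they count the same patients. Resistance is tested only in patients who fail (6.6.1, 8.1.2), so it concerns those patients too. Week-48 viral load is the only candidate that does not rest on the failure event.

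**Step 2. Which failures have a week-48 value?** Visits are at weeks 4, 12, 24, 36 and 48 (5.6, 8.3), so the gaps are 8, 12, 12 and 12 weeks. A patient leaves once failure is confirmed (6.6), and no later measurement is described.

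| First high value | Confirmed at next visit (6.6) | Confirmed within 1 month (8.1.1, 8.1.3) |
|---|---|---|
| Week 4 | leaves at 12, no week-48 value | leaves before 12, no week-48 value |
| Week 12 | leaves at 24, no week-48 value | leaves before 24, no week-48 value |
| Week 24 | leaves at 36, no week-48 value | leaves before 36, no week-48 value |
| Week 36 | confirmed at 48, value present | leaves before 48, no week-48 value |
| Week 48 | cannot be confirmed at a scheduled visit | needs a repeat after week 48 |

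Of the four onset visits before week 48, three have no week-48 value under 6.6 and all four have none under 8.1.1 and 8.1.3. Since every gap is at least 8 weeks, the one-month definition needs an unscheduled repeat at every visit, not only at week 48.

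**Step 3. How far do the two measures overlap?** Overlap = patients counted by both ÷ patients counted by either, comparing confirmed failure at any time with a value above 50 copies/mL at week 48. The rates are assumptions, because the protocol gives none: sustained rebound 5–20% over 48 weeks (constant hazard), isolated high values 0–6% per visit, and prompt repeat of each high value. Each scenario simulated 400,000 patients.

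| | Repeat after week 48 | No repeat after week 48 |
|---|---|---|
| Failing patients leave (6.6) | 13–25% | 0% |
| Failing patients stay and are measured | 45–100% | 32–77% |

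With 10% rebound, 3% isolated high values, departure at failure and a repeat after week 48, 10.4% of patients have confirmed failure. Only 5.5% of those still observed at week 48 have a value above 50, and overlap is 19%.

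**Step 4. What does the completer restriction do?** Suppose 10% of an arm fails: 0.10 × 20 = 2 patients. In all randomised patients the failure percentage is 2/20 = 10%. If both leave before week 48, the completers show 0/18 = 0%. One patient is 1/20 = 5 percentage points.

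**The case against.** The strongest reply is that 8.1.1 and 8.1.2 list what is measured and 8.1.3 lists what is derived from it. Viral load is then the measurement, failure is its endpoint, and the week-48 phrase is loose wording. The failure definition under 8.1.1, Hypothesis 1 (rates of suppression) and the interim rule in 6.5 (rates of virological failure) all favour that reading. It is reasonable and supports the fix below, but it does not fully reconcile the text: 8.1.1 still fixes a time point, resistance is still secondary in one list and primary in another, and 12.2 still analyses a slope in completers.

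Second, this is an exploratory pilot meant to inform later, adequately powered trials (12.4), and is not set up to be decided by one test. That stands and lowers the severity. It does not remove the need to say which result is primary in a randomised comparison.

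Third, the overlap figures depend on assumed rates, on cutting viral load at 50 copies/mL when 12.2 works on the log10 scale, and on whether high values at week 48 are repeated. That also stands; Step 2 needs no assumed rates.

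Three stronger readings are tempting, but the documents do not support them. A reader might infer that all four candidates count different patients; the three in 8.1.3 share one event. A reader might infer an inflated type I error from several primary endpoints; the protocol states no alpha and no rule that success on any one endpoint suffices. A reader might put a frequency on the measures pointing in opposite directions; that would depend on event rates the protocol does not give.

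**Conclusion.** The inconsistency is real and should be corrected, at moderate severity. Sections 1.14, 8.1.1, 8.1.2, 8.1.3 and 12.2 do not identify one primary comparison, and the stated principal variable differs in kind from the endpoints of the primary objective. Given departure at failure (6.6) and the completer analysis (12.2), week-48 viral load misses failures from three or four of the four onset visits before week 48, depending on the definition. Under the assumed rates, overlap with confirmed failure is 13–25% if values at week 48 are repeated afterwards and 0% if they are not. If failing patients were still measured at week 48, overlap would rise to 32–100%, so the size of the gap rests on 6.6 and 12.2 being applied as written. At 5 percentage points per patient, the choice of measure can change the headline of the pilot. Naming the primary endpoint belongs in the protocol even if a separate analysis plan exists.

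**What to change.** - In 1.14, 8.1.1 and 8.1.3, name one primary endpoint and contrast: the percentage with confirmed virologic failure through week 48, etravirine minus control, in all randomised patients. It is already the first endpoint listed in 8.1.3, and the interim rule in 6.5 also uses failure rates.
- Label time to failure, week-48 viral load and resistance at failure as supportive, and align 8.1.2 with that.
- Amend 12.2 so that this comparison is the primary analysis and is not restricted to completers. Without this change, a primary endpoint in all randomised patients would contradict 12.2.
- Reconcile the failure definitions in 6.6 (consecutive visits) and in 8.1.1 and 8.1.3 (within one month), so that departure from the study and the endpoint refer to a stated event.

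The cost is wording in these sections, with no extra patients. The sponsor gives up the freedom to headline another of the listed endpoints.

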### 8.1.2. Secondary Study Variables

- CD4+/CD8+ T lymphocytes count.
- Genotypic test if virologic failure occurs.
- Lipid profile: total, HDL-, LDL-cholesterol and triglyceride levels
- Administration of lipid-lowering drugs throughout the study (new administrations or the withdrawal of previous lipid-lowering drugs).
- Cardiovascular risk assessed by the SCORE equation
- Patient’s satisfaction assessed using a 100 mm analogue visual scale.
- Adverse events related to antiretroviral treatment (Toxicity)

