## 5.7. MASKING TECHNIQUE

Not applicable, since this has an open clinical trial design.

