**Secondary objectives:**

To compare the immunological efficacy of etravirine-based regimen with standard PI-containing regimens.

- Changes in CD4+/CD8+ T lymphocytes at week 48 from baseline.

To compare the tolerability and toxicity of etravirine-based regimen with standard PI-containing regimens.

- Changes in lipid parameters (total, HDL-, LDL-cholesterol and triglyceride levels) at week 48 relative to baseline values.
- Changes in the administration of lipid-lowering drugs throughout the study (new administrations or the withdrawal of previous lipid-lowering drugs).
- Percentage of patients who withdraw from the study.
- Percentage of patients who withdraw from the study due to toxicity.
- Percentage of patients with toxicity ≥ grade 3.

To compare the cardiovascular risk of etravirine-based regimen with standard PI-containing regimens.

- Changes in cardiovascular risk estimated by changes in the SCORE equation at week 48 relative to baseline values.

To compare patient’s satisfaction of etravirine-based regimen with standard PI-containing regimens.

- Changes in patient’s satisfaction at week 48 from baseline, using a 100 mm analogue visual scale.

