**Definitive:**

- A plausible time sequence exists in relation to administration of the drug or its plasma or tissue concentrations.
- The observed manifestation coincides with the known adverse reactions profile of the implicated drug.
- The event cannot be explained by the concurrent disease or by other drugs or chemical substances.
- Response to withdrawal must be clinically plausible, i.e., the condition improves on discontinuing administration of the drug.
- A positive response to repeat exposure is observed.

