## 9.3. PROCEDURE FOR REPORTING ADVERSE EVENTS

**The investigator:**

The investigator will immediately notify the study sponsor of any serious and/or unexpected adverse events (see section 9.1.).

The report will be realized during the first 24 hours since the start of the serious adverse event. Notification will be made by means of the adverse events reporting form contained in Appendix V of this protocol. This form will be sent to the sponsor by fax.

Adverse events identified in the course of a clinical trial are to be documented in the database (see Appendix I for CRD content).

All adverse events will be notified in table form in the final report of the clinical trial.

All adverse events will be recorded, regardless of the imputability (i.e., causal) relationship involved, in the corresponding adverse events description form. The latter is found in the CRF of each participant in the study (see Annex I).

Depending on the nature of the condition, each adverse event is to be classified as:

- serious / not serious
- unexpected / expected

The characteristics of the event, its seriousness and "expectability", determine when and how it is to be reported to the health authorities.

The recording of adverse events is the responsibility of the trial investigator team, which should indicate the time of appearance of the event (expressed in the shortest time unit possible), its serious / not serious status, and whether it was expected or unexpected. The intensity of the event (mild, moderate or severe) is to be specified, along with the measures adopted (none, treatment, exclusion), course (complete remission, partial remission, persistence) and imputability based on the criteria indicated in section 9.2.

Intensity will be assessed by the investigator using the following terms according to the OMS criteria:

- Grade I-II
- Grade III-IV

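### Two of the five tolerability and toxicity endpoints count only events that unblinded investigators judge treatment-related, so the grade 3 or higher comparison can be biased in either direction by attribution

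*Protocol*

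**What the plan says.** Section 8.1.2 lists among the secondary variables "Adverse events related to antiretroviral treatment (Toxicity)". This is the only place where the protocol says what toxicity means.

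Section 8.1.3 lists five endpoints for the tolerability and toxicity objective. Two rest on that word: "Percentage of patients with toxicity ≥ grade 3" and "Percentage of patients who withdraw from the study due to toxicity". The other three are "Changes in lipid parameters (total, HDL-, LDL-cholesterol and triglyceride levels) at week 48 relative to baseline values", changes in lipid-lowering medication, and "Percentage of patients who withdraw from the study" for any reason.

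On masking, section 5.7 says "Not applicable, since this has an open clinical trial design". Section 9.3 has the investigator team record each event with its severity and imputability. Section 9.2 gives five imputability categories, from definitive to unrelated, and does not say which of them count as related. The first criterion for the definitive category is "A plausible time sequence exists in relation to administration of the drug or its plasma or tissue concentrations".

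On data capture, section 9.3 says "All adverse events will be recorded, regardless of the imputability (i.e., causal) relationship involved". Section 12.3 plans a descriptive tabulation of all adverse events and a descriptive analysis of tolerability, laboratory tests included, in everyone enrolled.

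**The concern.** The named comparison of severe toxicity is a product of two things: how often severe events occur, and how often an investigator who knows the arm blames the antiretroviral regimen. Only the first is a property of the treatments.

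The design gives a reason why the second might not be equal. Under section 5.3 one arm starts etravirine at randomisation and the other stays on its regimen. Under section 6.2 antiretroviral therapy began at least 12 months before entry. The top three causality categories all ask for a time relation to drug administration, and the top two also ask for improvement on withdrawal. Investigators may find such criteria easier to meet for a drug started recently than for one taken for a long time.

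If that happens, the same event could count in one arm and not in the other. Comparing tolerability and toxicity is a stated secondary objective, and the severe-toxicity percentage is likely to be read as a summary of it.

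**Working it through.** The protocol gives no toxicity rate, no attribution share and no test for this endpoint, so there is no planned figure to reproduce. The check has two parts.

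**1. Which endpoints depend on attribution**

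- Toxicity of grade 3 or higher: yes, through the definition in 8.1.2.
- Withdrawal due to toxicity: yes, for the same reason.
- Lipid changes at week 48: no, a laboratory measurement.
- Changes in lipid-lowering drugs: no, a record of prescribing.
- Withdrawal for any reason: no, a count.

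Two of the five are affected.

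**2. How large the effect could be**

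Input from the protocol (sections 6.4 and 12.4): 20 patients per arm. Assumed inputs, not in the protocol: the same true all-cause rate *p* of grade 3 or higher events in both arms, 10 to 20%; share judged related *a* of 60 to 80% in one arm and *b* of 30 to 40% in the other. The shares are applied per patient, which is a simplification.

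Observed toxicity rate = *p* × share judged related. Spurious gap = *p* × (*a* − *b*). Gap in patients = 20 × gap.

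| Shares *a* / *b* | *p* = 10% | *p* = 15% | *p* = 20% |
|---|---|---|---|
| 60% / 40% | 2 points (0.4 patients) | 3 (0.6) | 4 (0.8) |
| 70% / 30% | 4 (0.8) | 6 (1.2) | 8 (1.6) |
| 80% / 40% | 4 (0.8) | 6 (1.2) | 8 (1.6) |
| 80% / 30% | 5 (1.0) | 7.5 (1.5) | 10 (2.0) |

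- Smallest: 0.10 × (0.60 − 0.40) = 2 points, or 0.4 patients.
- Largest: 0.20 × (0.80 − 0.30) = 10 points, or 2 patients.
- A middle case: 0.15 × 0.70 = 10.5% against 0.15 × 0.30 = 4.5%, or 2.1 against 0.9 patients.

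Swapping the shares between arms reverses the sign. Unequal attribution can also hide a real difference: true rates of 20% and 10% with shares of 40% and 80% give 0.20 × 0.40 = 8% and 0.10 × 0.80 = 8%. If the shares are equal, or if events of any cause are counted, the spurious gap is zero.

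What this does to the ranking of the arms, from exact binomials with 20 per arm, *p* = 20% and shares of 80% and 40%: the expected counts are 20 × 0.16 = 3.2 and 20 × 0.08 = 1.6. The arm with the higher share shows more toxicity with probability 71% and less with probability 15%. With equal shares of 80% the two probabilities are 41% each. A two-sided 5% test, which the protocol does not plan here, would flag the difference in roughly 12% of trials. The harm is therefore mainly a distorted descriptive estimate.

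**The case against.** The strongest reply is that the protocol already handles this. Events of every cause are recorded (9.3) and tabulated (12.3), and tolerability is described in all enrolled patients. A reader might infer from the endpoint definition that the all-cause comparison is lost. It is not. What stands is narrower: the endpoint named for comparing the arms is still the related-only one.

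A second reply is that the definition sits in a parenthesis in 8.1.2 and is not repeated in 8.1.3, where grade 3 or higher could be read as severity alone. That reading is possible, but 8.1.2 is the only definition given. If the sponsor meant severity alone, the wording needs the same repair.

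A third reply concerns the mechanism, and much of it stands. A reader might infer that attribution does differ and counts against etravirine. The protocol does not support this:

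- The time criterion quoted from the definitive category also allows a relation to drug concentrations, which a drug taken continuously can meet. The probable and possible categories ask only that the sequence be reasonable.
- Those three categories also require a match with the drug's known side effects, which does not favour either arm in any obvious way.
- The definition refers to antiretroviral treatment as a whole, and both arms take NRTIs.
- Patients can qualify under 6.2 through dyslipidaemia ascribed to their PI or gastrointestinal complaints ascribed to their antiretrovirals. Control patients who enter this way stay on a regimen already held responsible, which could raise attribution in that arm.

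A reader might also infer that the whole tolerability objective turns on unblinded judgement. Three of its five endpoints do not.

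**Conclusion.** The point holds as a minor one. As defined, the comparison of grade 3 or higher toxicity and of withdrawal due to toxicity depends on open-label causality judgement without a stated cut-off, in a design where the two arms differ in how recently the drug was started. Attribution could differ between arms and create, enlarge or mask a difference. That it does differ is an inference, and neither its direction nor its size can be taken from the protocol.

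Under the assumed ranges the spurious gap is 2 to 10 points, about 0.4 to 2 patients per arm of 20. That is enough to change which arm looks worse in a small table, but not a demonstrated bias. It concerns two secondary, descriptive endpoints in a 40-patient pilot and leaves the primary virological comparison untouched.

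**What to change.** In sections 8.1.2 and 8.1.3, make the comparative endpoint the percentage of all randomised patients with any new or worsened adverse event or laboratory abnormality of grade 3 or higher, whatever its cause. Measuring against baseline matters because patients can enter with laboratory abnormalities.

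Keep the related events as a supportive table and state which imputability categories in 9.2 count as related. Read withdrawal due to toxicity beside withdrawal for any reason, which is already an endpoint.

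The cost is wording. The events are already recorded under 9.3 and tabulated under 12.3, so no visits, patients or assessments are added. The severity bands in 9.3 already separate grades III-IV from I-II. The downside is that events unrelated to treatment add some noise, which matters somewhat with 20 per arm; the supportive table of related events shows how much of the total they make up.
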